### Exclusion Criteria

Failure to Obtain Informed Consent;Pregnant or Lactating Women; Or Have a Pregnancy Plan Within a Month After the Study (Including Male Subjects);Researchers' Family Members who Are Directly Involved in the Study;Patients Are Expected to die Within 48 H After Enrollment, Defined as Patients With Norepinephrine Usage at a Dose of 25 mg/min or More Under Full-Fluid Resuscitation, With a Systolic Blood Pressure <90 mm Hg and Serum pH Values <7.0. The Judgment Will be Made by the Treating Physician.

Informed consent should be sought for each participant or a patient's relative. They are free to withdraw from the study for any reason without the need for further explanation. This prospective observational study examines clinical outcomes in early HTG-AP patients with worrisome features treated with TG lowering therapy (from fasting to sophisticated blood purification). Therefore, no mandatory intervention or randomization is proposed. The main treatment modalities for TG-lowering therapy include fasting, medical treatment (either heparin, insulin, or both), and blood purification, including hemoperfusion, hemofiltration, and therapeutic plasmapheresis. The treatment is at the discretion of treating physicians.

We recommend all patients receive standard treatment that follows the “Acute Pancreatitis Treatment Guidelines” issued by the American College of Gastroenterology (ACG) in 2013 and the standard treatment plan for acute pancreatitis provided in the “Evidence-Based Guidelines for the Treatment of Acute Pancreatitis” issued by the International Association of Pancreatology (IAP) and the American Pancreatic Association (APA) (23, 24).

### Primary Outcome Measure

The primary outcome is organ failure (OF) free days to 14 days after enrollment. Only the final period of OF-free days is included, and patients who have OF at day 14 or died before day 14 are assigned to zero OF-free days.

Secondary outcome measures

Part I: Secondary outcomes during the index admission

New-onset organ failure;New-onset multiple-organ failure (MOF);New-onset persistent organ failure (POF);New receipt of organ support;Requirement of ICU admission;ICU free days to day 14;Hospital free days to day 14;

Part II: Secondary outcomes within 60 days after enrollment

Mortality censored at 60 days after enrollment;AP severity grade (Based on the Revised Atlanta Classification);Incidence of infected pancreatic necrosis (IPN);Incidence of septic shock;Incidence of abdominal bleeding;Incidence of gastrointestinal fistula.

### Definition of Outcomes

An individual SOFA score of 2 or more for the respiration, cardiovascular, or renal system is defined as the presence of organ failure. New-onset organ failure is defined as organ failure that is not present at any time in the 24 h after enrollment. Multiple organ failure is defined as two or more organ failures present at the same time. Persistent organ failure is defined as organ failure that persists for more than 48 h. ICU free days to day 14 after enrollment is defined as the number of days alive and not admitted to an ICU after the patient's latest discharge from the ICU before day 14. If the patient is admitted to an ICU on day 14 or dies prior to day 14, ICU-free days will be 0. Hospital-free days to day 14 after enrollment is defined as the number of days alive and not admitted to the hospital after the patient's final discharge from the hospital before day 14.

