### Inclusion Criteria

1. Age Between 18 and 70 Years old;2. Within 72 H From the Onset of Abdominal Pain;3. Symptoms and Signs of AP Based on Abdominal Pain Suggestive of AP, Serum Amylase at Least three Times the Upper Limit of Normal, and/or Characteristic Findings of AP on Computed Tomography or Less Commonly Magnetic Resonance Imaging (MRI) or Transabdominal Ultrasonography According to the Revised Atlanta Criteria (21).4. When Enrolled, TG > 1,000 mg/dL (11.3 mmol/L), Accompanied by the Clinical Features of any one or More of the Following (22):1) Signs of hypocalcemia (calcium levels < 2 mmol/L);2) Lactic acidosis (Lactate levels more than 2 mmol/L and PH < 7.35);3) The systemic inflammatory response syndrome (SIRS) is clinically recognized by the presence of two or more of the following:a) Temperature >38.5°C or <35.0°C;b) Heart rate of >90 beats /min;c) Respiratory rate of >20 breaths/min or PaCO2 of <32 mmHg;d) WBC count of >12, 000 cells/mL, <4,000 cells/mL, or >10 percent immature (band) forms;4) Organ failure defined by the sequential organ failure assessment (SOFA) score for respiration, renal and cardiovascular systems.

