### Statistical Analysis

Continuous normally distributed data were reported as means with SDs. Skewed continuous data were reported as medians and interquartile ranges (IQRs). Categorical data will be summarized by counts and percentages. The intergroup difference will be compared by Student's *t*-test or Wilcoxon rank-sum test for continuous variable depending on their normality and chi-square test for categorical data.

To evaluate the association between TG decline and OF free days, the study patients will be dichotomized depending on whether the TG level reaches 5.65 mmol/L on Day 3 (the day of enrollment is labeled Day 1, the next day labeled Day 2, and the following day Day 3). For the primary outcome comparison, Wilcoxon rank-sum test will be employed. However, since OF could be evaluated with a time-to-event analysis censored at 14 days to account for the mortality as a competing event, Fine and Gray competing risk regression is used to assess the group difference as a supportive analysis.

For the association between different TG lowering therapy and OF free days, we considered the possibility that baseline characteristics, which were expected to be prognostic for OF, differ according to the choice of TG lowering therapies (i.e., blood purification treatment and medical treatment). A propensity score matching will be further used to compensate for the intergroup unbalance.

For secondary outcomes, a multivariate analysis generalized linear model (GLM) model will be performed to identify its association with TG decline and TG-lowering therapy with proper link and distribution function. The variable included in the model will be age, sex, TG level at enrollment, and other baseline variables that have significant differences between groups.

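### No at-risk population is set for the new-onset outcomes, although patients already in organ failure are eligible and their early failure cannot count as new

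*Protocol article*

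**What the plan says.** All places are in the protocol article.

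- **Inclusion Criteria, item 4.** One of the four features that qualify a patient is "Organ failure defined by the sequential organ failure assessment (SOFA) score for respiration, renal and cardiovascular systems". Patients already failing are part of the intended cohort.
- **Definition of Outcomes.** The threshold is set by organ system: "An individual SOFA score of 2 or more for the respiration, cardiovascular, or renal system is defined as the presence of organ failure". For the new-onset outcomes, "New-onset organ failure is defined as organ failure that is not present at any time in the 24 h after enrollment". Also, "Multiple organ failure is defined as two or more organ failures present at the same time"; POF is failure lasting beyond 48 h.
- **Secondary outcomes, Part I (under Primary Outcome Measure).** The list opens with "New-onset organ failure;New-onset multiple-organ failure (MOF);New-onset persistent organ failure (POF);New receipt of organ support". No restricted population is attached to any of the four.
- **Statistical Analysis.** Patients are split by "whether the TG level reaches 5.65 mmol/L on Day 3". "For secondary outcomes, a multivariate analysis generalized linear model (GLM) model will be performed to identify its association with TG decline" and with TG-lowering therapy. The covariates fixed in advance are age, sex and TG at enrolment; any other baseline variable enters only if it differs significantly between the groups.
- **Study Objectives.** Secondary endpoints are described as hypothesis-generating.

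**The concern.** Eligibility deliberately includes patients in organ failure, while the definition of new-onset failure rules out whatever was seen in the first 24 h. The article does not say how a patient who falls under both is handled.

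Three invented patients show the problem, on a per-patient reading with everyone analysed:

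1. Enters with respiratory failure that lasts 10 days: new-onset OF no, new-onset POF no.
2. Enters with SIRS only and never fails: no, no.
3. Enters with SIRS only and has renal failure on Days 3 to 6: yes, yes.

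The first patient is scored like the second. Neither the TG groups nor the therapies are randomised, so the share with early failure may well differ between them. That difference alone would move the new-onset comparison. The study's rationale leans on earlier findings about POF, and supplying data for future trials is a stated objective, so distorted event rates here could be carried forward.

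**Working it through.** **The plan's own figures.** The article gives no event rate, share with early failure, or power for the new-onset outcomes. Its only power statement (87% and 82.5% with 240 evaluable patients) concerns OF-free days. It reproduces at 87.0–87.3% and 82.5–82.8%, assuming two equal groups and two-sided 5%, and does not bear on this point. Every rate below is therefore an assumption.

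**Formula.** Let b be the share of a group with organ failure in the first 24 h, r the risk of new-onset failure in patients free of it, and q the chance that a patient already failing is still counted as an event. Then

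all-patient risk = (1 − b) × r + b × q.

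Ratios are target reached over target not reached.

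**Per-patient reading (q = 0), equal true risk.** r cancels:

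- b 20% v 40%: 0.80/0.60 = 1.33
- b 30% v 40%: 0.70/0.60 = 1.17
- b 30% v 50%: 0.70/0.50 = 1.40

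**Per-patient reading, true at-risk ratio 0.70 (21% v 30%).**

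- b 20% v 40%: (0.21 × 0.80)/(0.30 × 0.60) = 0.168/0.180 = 0.93
- b 30% v 50%: (0.21 × 0.70)/(0.30 × 0.50) = 0.147/0.150 = 0.98

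A more extreme case reverses the sign. True risks of 15% v 25% (ratio 0.60) with b 20% v 60% become 0.15 × 0.80 = 12% v 0.25 × 0.40 = 10%, a ratio of 1.20.

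Restricting the analysis to patients free of failure through 24 h returns the true ratio in every case.

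**Per-system reading (q above 0), r = 20% in both groups, b 20% v 40%.**

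| q | Target reached | Not reached | Ratio |
|---|---|---|---|
| 0% | 0.16 + 0.00 = 16% | 0.12 + 0.00 = 12% | 1.33 |
| 10% | 0.16 + 0.02 = 18% | 0.12 + 0.04 = 16% | 1.13 |
| 20% | 0.16 + 0.04 = 20% | 0.12 + 0.08 = 20% | 1.00 |
| 30% | 0.16 + 0.06 = 22% | 0.12 + 0.12 = 24% | 0.92 |
| 40% | 0.16 + 0.08 = 24% | 0.12 + 0.16 = 28% | 0.86 |

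The distortion vanishes at q = r and reverses when q exceeds r.

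**Scope.** On the per-patient reading b is the same for new-onset OF and new-onset POF. For MOF and organ support, b would have to be the share already in MOF or already on that support, so the ratios above do not transfer to them.

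**Would the covariate rule catch the imbalance?** Take 120 per group (240/2, equal split assumed) and a two-sided 5% test of two proportions. With pooled proportion p, power = Φ[(difference − 1.96 × √(2p(1 − p)/120)) / √((b₁(1 − b₁) + b₂(1 − b₂))/120)].

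- 20% v 40%: (0.20 − 0.1160)/0.0577 = 1.46, so about 93%
- 30% v 40%: (0.10 − 0.1207)/0.0612 = −0.34, so about 37%

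A 30% v 40% imbalance, which already gives 1.17 with no true effect, would usually go unadjusted.

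**The case against.** A reader might infer that the plan keeps patients with early failure in the denominator and codes them as having no event. The article says neither that, nor that they are left out. Restricting each outcome to patients at risk is compatible with its definition, and the analysis population of a secondary outcome may be set in a full protocol or SAP that is not shown. This stands, and it makes the size of the problem conditional.

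A reader might also infer that the group with more baseline failure must look better. That does not follow. Organ failure is defined by system, so a patient with one failed system can still develop failure in another, and a patient with single-organ failure can still develop MOF. As the table shows, the distortion may then disappear or run the other way.

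The covariate rule is a partial safeguard. SOFA on admission is collected, and a large imbalance would probably bring it into the model. For moderate imbalances that is left to chance.

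Finally, ongoing failure is penalised in the primary outcome, where OF at day 14 or earlier death scores zero, and the secondary endpoints are exploratory. Both are true and limit the weight of the point.

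What remains is more than a detail deferred to another document. The article itself defines new-onset failure, admits patients to whom that definition applies awkwardly, and states a covariate rule that leaves baseline organ failure to a significance test.

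**Conclusion.** The point holds as a gap in how the new-onset outcomes are fixed. No at-risk set is named, per-patient or per-system judgement is not stated, and baseline organ failure is not a fixed covariate. If all patients are analysed on a per-patient reading, assumed early failure of 20% v 40% turns no effect into a ratio of 1.33, 30% v 40% gives 1.17, and a true 0.70 is diluted to 0.93 at 20% v 40%. These figures need four conditions: unequal early failure, an all-patient denominator, no event possible in those already failing, and no adjustment. The shares and risks are assumptions, because the article gives none. On a per-system reading the direction is open.

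Only secondary, hypothesis-generating outcomes are touched; nothing here supports a claim of bias in the primary outcome. This is a cheap improvement worth making.

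**What to change.** In Definition of Outcomes and Statistical Analysis:

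1. State whether new-onset is judged per patient or per organ system.
2. Analyse each outcome only in patients at risk of it at the end of the 24 h window:
   - New-onset OF and POF: on a per-patient reading, patients with no failure in the window. On a per-system reading, keep patients with a failed system who can still develop failure in another.
   - New-onset MOF: patients not in MOF.
   - New organ support: patients not already on that support.
3. Report the number at risk by group for each outcome.
4. Include baseline organ failure or SOFA as a fixed covariate whatever its significance. Where the at-risk set contains nobody with failure, the SOFA score is the usable form.

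An all-patient summary of any POF to day 14, new or continuing, adjusted for organ failure at enrolment, would be a useful but optional addition.

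No new data are needed, since admission SOFA, daily SOFA and daily major treatment are already collected. The cost is precision. With an assumed 20% v 40% early failure in two groups of 120, the per-patient at-risk set is 96 + 72 = 168 of 240 patients, and intervals widen accordingly.

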## Methods

### Study Objectives

The primary objective of the study is to evaluate the relationship between TG decline and the evolution of organ failure in a cohort of early HTG-AP patients with worrisome features. The secondary objectives are to characterize the current clinical practice regarding TG-lowering therapy, describe the association between different choices of therapy and clinical outcomes. The third objective is to provide data for future trials. Accordingly, every secondary endpoint is also supposed to be hypothesis generating.

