### Sample Size Justification

Based on the feasibility and patient flow of the participating sites, a sample size of 300 patients was expected, with an average of 15 patients per month within 2 years. Considering an estimated 20% rate of incomplete data or losses of follow-up, our expected sample size (240 patients) would provide 87% to detect a 2-days (SD: 5) or 82.5% for 1.5-days (SD: 4) improvement of organ failure free days between patients achieve target TG and those not.

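### Hospital-free days lacks the zero rule that ICU-free and OF-free days carry, so a patient discharged alive who dies before day 14 can outscore a survivor

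*Protocol article*

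**What the plan says.** All three free-day outcomes run to day 14 after enrollment.

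- **OF-free days (primary).** Protocol article, Primary Outcome Measure: "patients who have OF at day 14 or died before day 14 are assigned to zero OF-free days".
- **ICU-free days (secondary).** Protocol article, Definition of Outcomes. After a definition that counts days alive outside the ICU following the latest ICU discharge, the text adds: "If the patient is admitted to an ICU on day 14 or dies prior to day 14, ICU-free days will be 0".
- **Hospital-free days (secondary).** Same section, next sentence: "Hospital-free days to day 14 after enrollment is defined as the number of days alive and not admitted to the hospital", counted "after the patient's final discharge from the hospital before day 14". The section ends there.

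No other section of the article gives a rule for death, or for being an inpatient on day 14, for hospital-free days. Study Objectives sets the weight of the secondary outcomes: "every secondary endpoint is also supposed to be hypothesis generating". Deaths after discharge are followed up through the separate outcome "Mortality censored at 60 days after enrollment".

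**The concern.** A free-day outcome combines survival and length of stay in one number. It orders patients sensibly only if death is placed at or below the worst result for a survivor. The article does this for two of its three free-day outcomes. On the third, a patient who leaves hospital and dies within the window keeps credit for the days between discharge and death, so an early discharge that ends in death can score higher than a long stay that ends in recovery. The same missing sentence leaves open what a patient scores who was discharged, readmitted, and is an inpatient on day 14.

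Statistical Analysis models the secondary outcomes with a generalized linear model, so these values would enter the model as they stand. At stake is the meaning of one secondary outcome for a limited set of patients.

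**Working it through.** **1. The plan's own figure.** The article gives no figure for hospital-free days. Its only related figure is the power statement for OF-free days (Sample Size Justification): "our expected sample size (240 patients) would provide 87% to detect a 2-days (SD: 5) or 82.5% for 1.5-days (SD: 4) improvement". The evaluable number is 300 × (1 − 0.20) = 240. Assuming 120 per group and a two-sided 5% level, neither of which is stated, the noncentral t calculation gives 87.0% for 2 days (SD 5) and 82.5% for 1.5 days (SD 4). The stated power is reproduced. It concerns a different outcome, one that has its own zero rule, so nothing below changes it.

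**2. Does the phrase about days alive already imply zero?** The ICU definition uses the same phrase, and the authors still added an explicit zero for death. Read consistently, the phrase stops the count at death but does not erase the days already counted.

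**3. Scores under the written definition.** Counting whole days, for a patient discharged before day 14:

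hospital-free days = min(14, day of death) − day of final discharge

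A patient not discharged before day 14 has no qualifying days and scores 0. That zero is implied, not stated.

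| Patient | As written | With the ICU-type zero rule |
|---|---|---|
| Discharged day 4, dies day 9 | 9 − 4 = 5 | 0 |
| Discharged day 3, dies day 13 | 13 − 3 = 10 | 0 |
| Discharged day 5, dies day 6 | 6 − 5 = 1 | 0 |
| Dies in hospital day 8, never discharged | 0 | 0 |
| Survivor, in hospital on day 14, never discharged | 0 (implied) | 0 |
| Survivor, discharged day 10 | 14 − 10 = 4 | 4 |
| Discharged day 4, readmitted day 10, in hospital day 14 | can be read as 10 − 4 = 6 | 0 |

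The first patient (5) ranks above the survivor still in hospital (0) and above the survivor discharged on day 10 (4). With the zero rule, every death before day 14 ties with a survivor still in hospital and ranks below any survivor who was discharged before day 14 and stayed out.

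**4. Size.** If k affected patients each carry s surplus days in a group of n, the group mean moves by k × s / n. The documents supply neither k nor s. For illustration only, assume 1–3% of 240 (about 2 to 7 patients), 5 days each, all in one group of 120: 2 × 5 / 120 = 0.08 to 7 × 5 / 120 = 0.29 days. Split evenly between two equal groups, the net difference is about zero. These values show scale under assumptions; they are not estimates for this study.

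**The case against.** The strongest reply is that the gap is narrow and of low weight. The count starts only at final discharge, so a death in hospital without earlier discharge already scores 0, as does a survivor never discharged by day 14. What is left is patients discharged alive who die before day 14, plus the readmission case. The outcome is one of several hypothesis-generating secondary outcomes, it is listed among those of the index admission, and mortality to day 60 is reported separately, so these deaths stay visible. All of this stands and limits the weight of the point.

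It can also be said that a journal article condenses a fuller protocol, which may contain the missing sentence. That is possible. But the definition is printed as a complete statement directly after a parallel one that does carry the rule, so this is an inconsistency within the article and not a detail it merely leaves out.

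Three stronger readings are tempting and are not supported:

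- **A sizeable shift in group means.** Taking 13 surplus days for each of 2 to 7 patients, all in one group of 120, gives 2 × 13 / 120 = 0.22 to 7 × 13 / 120 = 0.76 days. This combines an assumed rate, a ceiling score that needs discharge almost at enrollment and death almost at day 14, and complete concentration in one group.
- **Bias between exposure groups.** A reader might infer that discharge shortly before death follows severity and hence triglyceride decline. Nothing in the article describes or quantifies such a link.
- **Harm from non-comparable outcomes.** The article does not pool the three free-day outcomes or rank them against each other, so the difference in rules has no consequence of that kind.

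**Conclusion.** The point holds as a minor inconsistency of definition. Followed literally, the hospital-free-days rule gives a positive score to a patient discharged alive who dies before day 14, and can do so for a patient who is back in hospital on day 14. The article's two sister outcomes give zero in the matching situations. The reversed ordering follows from the text alone and, for the deaths, always runs in favour of the patient who died.

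The number of patients affected is probably small, but the documents give no rate; any effect on group means or on the contrast between exposure groups is unknown. The conclusion rests on two readings: that days alive ends the count at death without setting it to zero, and that a patient never discharged before day 14 scores 0. The primary analysis and the sample-size statement are unaffected.

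**What to change.** Add one sentence after the hospital-free-days definition, mirroring the one for ICU-free days: hospital-free days are set to 0 for any patient who is an inpatient on day 14, or who has died before day 14, whether in or out of hospital.

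This needs no new data. Mortality, vital status and hospital days are already collected (Data Collection and Management; Table 1). The existing definition already requires the date of death, to count days alive, and the date of final discharge; the zero rule needs only whether death came before day 14 and whether the patient was in hospital that day. It places such a death level with a survivor still in hospital, not below, which is how the article already treats death in its other two free-day outcomes. If the full protocol or analysis plan already contains the sentence, the only change is to confirm that it governs.
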